#### Cost-effectiveness: base-case analyses

The probability of the two eHealth PPI conditions (arm 1 or arm 2) being cost-effective compared to TAU (arm 3) will be calculated from a societal perspective. Following the Dutch guidelines for economic evaluation in healthcare [65, 66], costs and effects extending beyond a 1-year follow-up period will be adjusted to their present value by an annual discount rate of 3% and 1.5%, respectively. In addition, all costs will be indexed to the most recent base year deemed appropriate. An additional scenario may be considered, assuming that costs and effects within and beyond the 1-year follow-up period should be adjusted to their present value. In addition to performing an ITT-analysis of cost-effectiveness, a complete-case cost-effectiveness analysis will be employed, using only data from participants who completed all measurements. Baseline differences in costs and outcomes between the trial arms will be analyzed and, if necessary, accounted for using regression analysis [101].

In the proposed cost-effectiveness analysis (CEA) and cost-utility analysis (CUA), the incremental cost-effectiveness ratio (ICER) will be calculated to facilitate two pairwise comparisons: (I) arm 1 vs. arm 3, and (II) arm 2 vs. arm 3. For both comparisons, the ICER represents the difference in societal costs between an eHealth PPI condition (arm 1 or arm 2) and the TAU condition (arm 3), divided by the corresponding difference in clinical outcomes (e.g., QALYs and MHC-SF scores). The robustness of the ICERs obtained will be assessed through non-parametric bootstrapping, using 1000 samples. This approach aims to predict the joint distribution of costs and effects within a cost-effectiveness plane (CE-plane) [102].

Subsequently, the cost-effectiveness of the two eHealth PPI conditions compared to TAU depends on the willingness to pay (WTP) for an incremental gain in effectiveness associated with a new treatment [100]. In the Dutch healthcare system, WTP thresholds of €20,000, €50,000 and €80,000 per QALY gained exist, depending on the burden of disease [65, 66]. Based on the Integrated Disease Burden Calculator (IDBC) [103], a WTP of €20,000 per QALY gained may be considered an appropriate threshold. All assumptions for this calculation are provided in Appendix 1. Using a WTP continuum ranging from €0 to €80,000, a cost-effectiveness acceptability curve (CEAC) will be presented, displaying the likelihood that the bootstrapped ICERs of both PPI conditions compared to TAU fall below the assumed WTP threshold of €20,000 per QALY gained. This method reflects the probability that either of the two eHealth PPI conditions (arm 1 or arm 2) is cost-effective compared to TAU (arm 3). Using the same CEAC, the probability of arm 2 being cost-effective compared to arm 1 - and vice versa – will also be computed. To address uncertainties affecting the base-case analyses, the ICERs obtained will be recalculated using sensitivity analyses on the parameters of costs and health service use [104].

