#### Study 2: randomized controlled trial design

A three-arm RCT design will be implemented to examine the (cost-)effectiveness and procedural implementation of the eHealth PPI for patients awaiting mental health treatment without loved ones (arm 1) and in patients awaiting mental health treatment with their loved ones (arm 2), compared to patients not receiving the eHealth PPI during their waiting period for mental health treatment (TAU in arm 3). Following study enrollment, all participating patients will be assigned to one of the three RCT arms, using simple randomization with an equal 1:1:1 allocation ratio. A loved one will be added to each patient in arm 2. Participants will receive seven different measurements: a pre-PPI measurement, immediate post-PPI measurement, 3-month post-PPI measurement, 6-month post-PPI measurement, 9-month post-PPI measurement, 12-month post-PPI measurement and a final 12-month measurement following treatment completion at a Dutch mental health clinic. The dependent primary outcome variable will be positive mental health, which consists of social, emotional, and psychological wellbeing [41]. Dependent secondary outcome variables include optimism, self-compassion, savoring, gratitude, resilience, quality of life and costs in psychiatric patients. Independent background characteristics include demographics (e.g., age, sex, education), clinical profile (e.g., severity of complaints) and expectations. A flowchart of the RCT is presented in Fig. 1 on page 13 below, displaying the primary and secondary outcomes for each measurement.

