#### A priori sample size

The a priori sample size in study 2 is based on the anticipated change in positive mental health between baseline and one-year treatment follow-up at the clinical setting in the intervention conditions compared to the control group. Compared to arm 3 (i.e., TAU), a medium effect size of Hedges’ g = 0.45 is assumed for both PPI arms followed by a mental health treatment (i.e., arms 1 and 2). The effect size of Hedges’ g = 0.45 is conservatively estimated based on prior studies about PPI effectiveness [21, 45], assuming an overlap in treatment mechanisms when combining a PPI with a subsequent mental health treatment. The Mental Health Continuum – Short Form (MHC-SF) is defined as the primary outcome [46], which is justified in the section on ‘’Data collection’’. Using a pretest-posttest design for this primary outcome, the required sample size was estimated at 207 patients, including 69 patients per treatment arm under a 5% Type I error rate, 80% statistical power, and an equal allocation ratio. While the PPI + mental health treatment arm including loved ones (arm 2) is expected to yield a larger effect size than the PPI + mental health treatment arm without loved ones (arm 1), the actual difference between both effect sizes is unknown due to the novelty of the inclusion of loved ones. In the absence of previous studies, we will conservatively assume identical effect sizes for both arm 1 and arm 2, which can be compared to arm 3 (TAU) with a sufficient degree of certainty. In addition, we still aim to compare arm 1 to arm 2 exploratively, knowing that these specific comparisons may not be adequately powered. Assuming a 35,5% attrition rate between baseline and the 1-year follow up measurement following treatment completion based on previous findings [47, 48], a total sample size of 207/(1–0.355) = 321 participants (*n* = 321) is required, yielding 107 patients per treatment arm. Since the second arm involves one loved one per patient, this arm will contain 214 participants. Thus, a total sample size of 428 participants will be required, including 321 patients and 107 loved ones.

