## Data analysis

All analyses of (cost-)effectiveness will be performed in accordance with the Intention-To-Treat (ITT) principles, meaning that data from all participants will be analysed according to the study condition to which they were initially assigned, regardless of adherence [94]. Assessment of baseline inequalities between study conditions will be performed and followed up, if needed. Due to the longitudinal nature of study 1 and study 2, dropout and other processes causing missing data are expected [95]. Appropriate missing data handling techniques will be applied after assessment of the magnitude, mechanisms, and patterns of missing data [96]. A one-sided alfa of 0.05 will be applied in both studies. Since multiple comparisons between RCT arms will be performed in study 2, this significance level of 0.05 will be adjusted to manage Type I error probability, using the Holm-Bonferroni method [97].

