### Clinical effectiveness

#### Primary analyses

The primary clinical analyses aim to examine whether the eHealth PPI has a significant clinical effect on positive mental health (i.e., MHC-SF), which will be evaluated in the RCT of study 2. The primary analysis will be an Analysis Of Covariance (ANCOVA), which aims to compare the three independent RCT conditions on positive mental health scores at the 12-month post-PPI measurement, with the pre-PPI measurement serving as a covariate.

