In study 2, multilevel regression modelling will be used to examine and compare the average longitudinal trajectory of change on the primary outcome (i.e., MHC-SF) across the three RCT arms. Based on theoretical considerations, certain demographics (i.e., education and literacy, employment status, sex, and age) and clinical profiles (i.e., severity of psychological complaints, and diagnosis) are considered relevant group-level moderators for modelling such change trajectories. Using these moderators in a multilevel regression model, moderation analyses will be employed to examine variations in longitudinal change trajectories between the RCT conditions on the primary outcome (i.e., MHC-SF) and relevant secondary outcomes (i.e., BSI, MHQoL, and BRS-NL) across the seven RCT measurement points. Using the same moderation analyses, the average trajectory of change for certain subpopulations will be examined across the seven RCT measurement points to evaluate how different subpopulations respond to the eHealth PPI over time. Notably, moderation analyses for subpopulations may reveal different associations between group-level moderators and PPI effectiveness, even if these associations cancel each other out in the overall change comparisons between the three RCT conditions [99].

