### Economic evaluation

#### Valuation of clinical outcomes

In the CEA of study 2, clinical outcomes derived from the MHC-SF, BSI and BRS-NL will be valued, using specific conversion guidelines [65, 66]. In the CUA of study 2, utility scores derived from the EQ-5D-5 L, MHQoL and ICECAP-A will be converted to QALYs using existing methods, including the area-under-the-curve method [100]. While the EQ-5D-5 L scores will serve as the main quality of life outcomes, the MHQoL and ICECAP-A scores will be used in a sensitivity analysis. In general, MHQoL and ICE-CAP-A scores are expected to reflect wellbeing differently in patients facing psychological complaint, when compared to EQ-5D-5 L scores [81].

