Apart from the anticipated strengths, certain operational challenges in performing the studies need to be addressed. Firstly, not all patients are equally knowledgeable about eHealth, neither are they equally literate. In fact, intervention adherence among participants may be compromised due to low eHealth literacy [111]. To address this challenge, an evaluation of implementation procedures will be conducted to examine and optimize the eHealth PPI from a user-perspective, using a variety of quantitative and qualitative approaches prior to and during both studies. Secondly, dropout among patients and loved ones may be related to the weekly 4-hour time investments required to complete an intervention module, the extensive measurements and confrontational questionnaires [112]. To mitigate this risk, precautionary measures will be taken to ensure that the time spent on each measurement will be at most 30 min. These measures include using brief, yet validated questionnaires addressing the research objectives. Thirdly, the two eHealth PPI arms (with and without loved ones) will be compared to each other exploratively in study 2, since there is no information about effect sizes available to perform a fully powered analysis. Until all data are collected, it remains unclear whether the sample size of study 2 is adequate for this purpose. In fact, the expected difference in effects between both PPI arms is likely smaller than the difference between each PPI arm and the TAU arm, which was considered the foundation for the a priori sample size calculation. If this turns out to be the case, the statistical power may fall below the conventional 80% threshold and true differences may remain undetected. In that case, any conclusions about the generalizability of upcoming findings should be drawn with greater caution. That being said, the interim analyses aim to estimate the actual effect size, which is informative for both PPI forms (with and without loved ones) in our research setting. More specifically, this estimation of the actual effect size may guide future research initiatives aimed at developing a confirmative study design employing both PPI forms with a sufficient degree of statistical power, without compromising the most important contrasts (i.e., PPI for patients vs. TAU and PPI for patients + loved ones vs. TAU). Fourthly, assessing (cost-)effectiveness may be complicated due to the heterogeneity of the target populations addressed in the current project. Apart from loved ones, various clinical patient populations are eligible for participation. Since clinical factors may substantially affect costs and treatment outcomes, certain clinical profiles (i.e., severity of psychological complaints, and diagnosis) will be included as covariates in both studies. Fifthly, the proposed recruitment procedures at the Dutch mental health clinic and the eHealth organization are aimed at minimizing selection bias, which may optimize the representativeness of vulnerable patient populations in our studies. However, a selectively induced bias among participants may not be ruled out entirely, since vulnerable target groups (e.g., individuals with low literacy) are less likely to seek psychological treatment and to participate in digital research [113, 114]. Lastly, the southern regions in the Dutch province of Limburg are characterized by significant socio-economic challenges [113], which could affect the broader generalizability of upcoming study findings on a national level in The Netherlands.

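### The base-case economic evaluation adjusts for baseline costs and outcomes only if inspection of the arms suggests it; adjustment should be fixed in advance

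*Protocol article*

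**What the plan says.** The rule for the economic evaluation stands under Cost-effectiveness: base-case analyses: "Baseline differences in costs and outcomes between the trial arms will be analyzed and, if necessary, accounted for using regression analysis". Other parts of the protocol article bear on it:

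- Table 2 schedules the EQ-5D-5L, TIC-P and MHC-SF for patients at T0 and at all six later measurements.
- Study 2: randomized controlled trial design assigns patients "using simple randomization with an equal 1:1:1 allocation ratio".
- Valuation of clinical outcomes states that "utility scores derived from the EQ-5D-5 L, MHQoL and ICECAP-A will be converted to QALYs using existing methods, including the area-under-the-curve method". The EQ-5D-5L is the main utility source.
- Cost-effectiveness: base-case analyses uses 1000 bootstrap samples and takes €20,000 per QALY as the assumed threshold.

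On the clinical side, Primary analyses specifies an ANCOVA of the 12-month MHC-SF, "with the pre-PPI measurement serving as a covariate". Data analysis adds a general sentence: "Assessment of baseline inequalities between study conditions will be performed and followed up, if needed". The Discussion says that "certain clinical profiles (i.e., severity of psychological complaints, and diagnosis) will be included as covariates in both studies". Under Secondary analyses the same variables, with several demographics, "are considered relevant group-level moderators for modelling such change trajectories".

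**The concern.** The base-case sentence is a stated rule and not a silence: look at the baseline differences, then decide whether to adjust. Two analysts following it could report different incremental costs and QALYs from the same data.

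The rule also misjudges when adjustment helps. Baseline utility is the first point of the area under the curve and predicts the later points, so a baseline gap shifts incremental QALYs whether or not it looks notable. The same holds for baseline costs and baseline MHC-SF to the extent that they predict follow-up. Adjustment also reduces residual variance when the arms happen to be balanced, and a conditional rule gives up that gain in most realised samples. At stake are the precision and reproducibility of the ICERs, the bootstrap cloud and the acceptability curve.

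**Working it through.** **Inputs from the protocol article**

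- Patients per arm: A priori sample size gives 207/(1 − 0.355) = 320.9, rounded to 321, and 321/3 = 107. This reproduces the stated figure.
- Patients per arm expected after attrition: 69 (same section).
- Visits: an eight-week intervention, then measurements immediately after it and 3, 6, 9 and 12 months later. T0 to T5 are taken as weeks 0, 8, 21, 34, 47 and 60.
- Threshold: €20,000 per QALY.

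**Assumptions, not in the document**

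- Exchangeable within-patient correlation ρ of 0.3, 0.5 or 0.7.
- Utility SD 0.25, with 0.20 as a check.

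**Step 1. Area-under-the-curve weights (trapezium rule, years).** They are 0.077, 0.202, 0.25, 0.25, 0.25 and 0.125. Their sum is S = 60/52 = 1.154, and the sum of their squares is 0.250.

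**Step 2. Dependence of the QALY on baseline utility (SD units).**

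- Variance of the QALY: (1 − ρ) × 0.250 + ρ × 1.154².
- Slope on baseline: 0.077 + ρ × (1.154 − 0.077).
- R² = slope² / variance. The SE under fixed adjustment is √(1 − R²) times the unadjusted SE.

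| ρ | Variance | Slope | R² | √(1 − R²) | SE reduction |
|---|---|---|---|---|---|
| 0.3 | 0.574 | 0.400 | 0.279 | 0.849 | 15% |
| 0.5 | 0.791 | 0.615 | 0.479 | 0.722 | 28% |
| 0.7 | 1.007 | 0.831 | 0.685 | 0.561 | 44% |

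The percentage reductions do not depend on the utility SD or on the number of patients.

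**Step 3. Effect of a chance gap.** The SE of the baseline difference is 0.25 × √(2/107) = 0.034. The expected shift in unadjusted incremental QALYs is slope × gap:

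- ρ = 0.3: 0.014 QALY, about €270.
- ρ = 0.5: 0.021 QALY, about €420.
- ρ = 0.7: 0.028 QALY, about €570.

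With SD 0.20 the amounts are about €220, €340 and €450. With SD 0.25 and 69 per arm the gap is 0.25 × √(2/69) = 0.043, and the amounts are about €340, €520 and €710.

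**Step 4. What a conditional rule recovers.** The article gives no criterion, so a 5% significance test of the baseline difference serves as one possible reading. This check uses a single follow-up measure, for which fixed adjustment multiplies the variance by 1 − ρ². At ρ = 0.5 and 107 per arm, a large-sample simulation (200,000 runs) gave these SDs of the estimated difference, in outcome SD units: 0.137 unadjusted, 0.132 with test-then-adjust and 0.118 with fixed adjustment. The conditional rule recovers (0.137 − 0.132)/(0.137 − 0.118), about a quarter of the gain. Its two-sided 5% error rate was 4.6%, 4.3% and 3.5% for ρ = 0.3, 0.5 and 0.7, so it is conservative and inefficient.

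**Step 5. The clinical passages side by side.** Primary analyses includes baseline MHC-SF without condition and names no other covariate. Secondary analyses uses severity and diagnosis as moderators in multilevel models. The Discussion calls them covariates in both studies, without naming a model.

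**The case against.** The article does plan regression adjustment for costs and outcomes. The criterion, covariate list and bootstrap handling commonly sit in a health-economic analysis plan that is not shown. This stands as far as missing detail goes, and none of that detail is counted as an omission here. It does not rescue the condition itself, which the article states.

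A reader might infer that the economic results will be biased, or the error rate inflated. The documents do not support this. Randomization keeps the unadjusted estimate unbiased on average, and a strict test-then-adjust rule is conservative. What remains is imbalance in the realised sample, lost precision and discretion.

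A reader might also infer that the primary clinical result suffers the same loss, or that its model is specified in two incompatible ways. That goes too far. The primary ANCOVA always includes baseline MHC-SF. The general sentence under Data analysis mentions neither adjustment nor choice of estimator. The Discussion sentence concerns heterogeneity, does not name the primary model, and cannot be a literal specification for both studies, since study 1 has ten participants and a descriptive visual analysis. It is loose wording that should be aligned.

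Finally, the utility SD, the correlations and the 5% screening rule are not in the documents. That is correct, so the size is given as a range and the screening result only as an illustration.

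**Conclusion.** The concern holds for the base-case economic evaluation. The adjustment rule depends on the data, although the baseline values needed for a fixed rule are already scheduled. Fixed adjustment for baseline utility would reduce the SE of incremental QALYs by roughly 15% to 44%. That range assumes exchangeable correlation between 0.3 and 0.7, the T0 to T5 horizon and complete data. The euro amounts rest further on the assumed utility SD and the number of patients analysed. The gain for costs and for MHC-SF effects follows the same logic but depends on correlations that the document does not give.

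This should be changed, but it does not threaten the validity of the trial. The mismatch between the Discussion and the analysis sections on severity and diagnosis is a separate, minor matter of wording.

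**What to change.** Under Cost-effectiveness: base-case analyses, delete the condition and state that adjustment is always made:

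- QALYs regressed on arm and baseline EQ-5D-5L utility;
- MHC-SF effects regressed on arm and baseline MHC-SF;
- costs regressed on arm and baseline TIC-P cost;
- each regression refitted within every bootstrap replicate.

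An unadjusted analysis can be kept as a labelled sensitivity analysis.

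Separately, bring the Discussion sentence on severity and diagnosis into line with Primary analyses (baseline MHC-SF as the covariate) and Secondary analyses (moderators in the multilevel models). Adding BSI severity to the primary ANCOVA is not required.

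The cost is wording and a few lines of analysis code. It needs no new measurements and no additional patients.

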**Discussion:**

Introducing a transdiagnostic eHealth PPI to various patients awaiting mental health treatment and their loved ones may improve treatment outcomes. Enhancing resilience through an eHealth PPI may reduce healthcare costs and health-related societal costs, potentially making it a cost-effective strategy compared to TAU.

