### Economic evaluation

#### The application of previously described clinical outcomes for the CEA

In the CEA of study 2, certain outcome variables for assessing clinical effectiveness will also be used to evaluate cost-effectiveness. In the CEA, the aforementioned measure for positive mental health (MHC-SF) will be defined again as the primary outcome. Secondary outcomes will include all scores obtained from the previously mentioned BSI and BRS-NL.

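### The stated rule for the probability of cost-effectiveness (bootstrapped ICERs below €20,000 per QALY) misclassifies every bootstrap sample with a QALY loss; it should be restated as net benefit

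*Protocol article*

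**What the plan says.** All of this is in the protocol article, section *Cost-effectiveness: base-case analyses*, unless another section is named.

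- The ICER is the difference in societal costs between a PPI arm and TAU, divided by the difference in outcome. It is bootstrapped with 1000 samples to obtain the joint distribution of costs and effects on a cost-effectiveness plane.
- On the threshold: "a WTP of €20,000 per QALY gained may be considered an appropriate threshold". The appendix derives this from a proportional shortfall of 0.26.
- On the range of the curve: "Using a WTP continuum ranging from €0 to €80,000, a cost-effectiveness acceptability curve (CEAC) will be presented".
- On the quantity that the curve is to show: "the likelihood that the bootstrapped ICERs of both PPI conditions compared to TAU fall below the assumed WTP threshold of €20,000". The threshold is expressed per QALY.
- On what the curve means: "This method reflects the probability that either of the two eHealth PPI conditions (arm 1 or arm 2) is cost-effective compared to TAU (arm 3").
- The same curve is then to supply the probability that arm 2 is cost-effective compared with arm 1, and the reverse.

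No section mentions quadrants, dominated samples or net monetary benefit. Savings are expected to be possible; the abstract says: "Enhancing resilience through an eHealth PPI may reduce healthcare costs and health-related societal costs".

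**The concern.** The article states a counting rule and says what the count measures, and the two disagree. An ICER below the threshold means good value only when the QALY difference is positive. With a negative QALY difference the same inequality means poor value.

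The probability of cost-effectiveness against TAU answers the primary economic objective, and the arm 2 against arm 1 probability answers the secondary one. The second comparison is the more exposed. The main Discussion expects the difference in effects between the two PPI arms to be smaller than either difference from TAU, so bootstrap samples on both sides of zero are more likely there. The section *Valuation of societal costs* expects higher intervention costs in arm 2.

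A pre-specified rule has to work when the hypothesis fails. Under a null or harmful QALY effect with extra cost, this one leans towards the PPI.

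**Working it through.** **1. The plan's own threshold.** From the appendix, QALYs without disease are 27.52 and with standard care 20.5. Shortfall = (27.52 − 20.5)/27.52 = 0.255, which rounds to the stated 0.26. This is below 0.4, so €20,000 per QALY follows. The threshold is not in question. The article states no probability of cost-effectiveness to reproduce.

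**2. Algebra.** Let dE be the QALY difference, dC the cost difference and λ = €20,000.

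- Stated rule: dC/dE < λ.
- Net monetary benefit (NMB) rule: λ·dE − dC > 0.
- If dE > 0, multiplying by dE keeps the inequality, so the rules agree.
- If dE < 0, multiplying by dE reverses it: dC/dE < λ becomes dC > λ·dE, which is NMB < 0.

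The misclassified share is therefore exactly the share of samples with dE < 0.

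| Sample | dE | dC (€) | ICER | Stated rule | NMB (€) | Correct |
|---|---|---|---|---|---|---|
| Better, dearer | +0.05 | +500 | 10,000 | yes | +500 | yes |
| Better, dearer | +0.02 | +1,000 | 50,000 | no | −600 | no |
| Better, cheaper | +0.03 | −500 | −16,667 | yes | +1,100 | yes |
| Worse, dearer | −0.03 | +500 | −16,667 | **yes** | −1,100 | no |
| Worse, small saving | −0.05 | −500 | 10,000 | **yes** | −500 | no |
| Worse, larger saving | −0.02 | −1,000 | 50,000 | **no** | +600 | yes |

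**3. Arm 2 against arm 1, and the reverse.** Swapping the arms changes the sign of both differences, and (−dC)/(−dE) = dC/dE. The stated rule therefore returns the same number in both directions: if one is 70%, so is the other. Under net benefit the two sum to 100%. This needs no assumed figures.

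**4. Size.** The documents give no SDs or expected differences for costs or QALYs, so these are assumptions: cost SD €5,000–10,000, QALY SD 0.15–0.25, correlation −0.2, bivariate normal differences, SE = SD × √(2/n). The 107 per arm is from the section *A priori sample size*. At the lower SDs, SE = 0.15 × √(2/107) = 0.0205 QALY and 5,000 × √(2/107) = €684.

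| True dE, dC | Stated rule | Net benefit |
|---|---|---|
| +0.06, −€500 | 86–98% | 85–98% (gap at most about 1 point) |
| +0.03, +€300 | 62–75% | 57–64% (gap up to 14 points) |
| +0.01, +€500 | 60–71% | 36–43% |
| 0, +€500 | 64–74% | 28–38% |
| −0.01, +€500 | 69–78% | 21–34% |
| +0.01, −€1,000 | 71–74% | 77–92% |

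One case split by quadrant (0 QALY, +€500, SDs €5,000 and 0.15):

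- Both rules accept 14% (better and cheaper) plus 9% (better and dearer, under the line).
- The stated rule adds 41% that are worse and dearer, and 4% that are worse with too small a saving: 14 + 9 + 41 + 4 = 68%.
- Net benefit adds instead the 5% that are worse with a large enough saving: 14 + 9 + 5 = 28%.

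At a WTP of €0, the lower end of the planned curve, the correct value is simply the probability of saving money. In this case that is 23%; the ratio rule gives 55%.

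**5. Sensitivity.** With 69 per arm (the complete cases planned), 0 QALY and +€500 gives 64–75% against 32–40%, and the gap at +0.06 QALY and −€500 is up to about 2 points. With correlation 0 and 107 per arm, 0 QALY and +€500 gives 59–71% against 27–37%.

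**The case against.** The strongest reply is that the sentence is shorthand. The article plans a cost-effectiveness plane and an acceptability curve, and such a curve is ordinarily the share of bootstrap samples on the acceptable side of the WTP line. It also speaks of willingness to pay for a gain in effectiveness, and a negative ratio arising from a QALY loss is not a cost per QALY gained. In a condensed article the classification of samples could be left to a fuller plan.

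This has force. A reader might infer that the trial will in fact count dominated samples as cost-effective. The documents do not support that: they neither say so nor exclude it. The reply does not rescue the sentence, however. The rule is stated, not omitted; a scatter on the plane does not change how samples are counted; and the literal rule cannot give a sensible answer for arm 2 against arm 1 in both directions.

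A second reply is that the error is small if the hypothesised benefit is real. That stands at a gain of 0.06 QALY. At 0.03 QALY with €300 extra cost the gap can reach 14 points, but both rules stay above 50%.

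A reader might also infer that the ICER for the BSI, a secondary outcome of the cost-effectiveness analysis on which lower scores are better, carries the wrong sign. That is not supported. The €20,000 threshold is per QALY and is not applied to the BSI, the section *Valuation of clinical outcomes* refers to conversion guidelines, and no section fixes the direction of coding.

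**Conclusion.** The rule is wrong as written, and the point is of moderate weight. Two parts rest on algebra alone: every bootstrap sample with a QALY loss is misclassified, and the two directions of the arm 2 against arm 1 comparison receive the same probability.

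The effect on the reported result depends on SDs and true differences that the documents do not give. Under the assumptions above it is about 1 point or less at +0.06 QALY with a €500 saving. It moves the result across 50% when the true QALY difference is near zero or negative and the PPI costs €500 more. A reader might conclude that the economic finding is liable to reverse in general. The figures do not support that: reversal needs a QALY difference near or below zero and a literal implementation of the sentence. In the case of +0.01 QALY with a €1,000 saving the stated rule understates the probability, but both rules favour the PPI.

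**What to change.** In *Cost-effectiveness: base-case analyses*, replace the description of the curve with a definition: at each WTP value from €0 to €80,000, the probability of cost-effectiveness is the share of bootstrap samples in which WTP × QALY difference − cost difference is above zero. Read the value at €20,000 from that curve. Use the same definition for arm 2 against arm 1. Report the share of samples in each quadrant of the cost-effectiveness plane beside it.

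The cost is a sentence or two of protocol or analysis-plan wording and one line of code. Design, sample size and data collection are unchanged. If the conventional rule was intended all along, the change only makes the text match it.
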